**Methods:**

This study is a prospective, phase III, randomized, double-blind, active-controlled, non-inferiority, four-parallel group, dose-titration, multicenter trial. We recruit patients with hypertensive diabetic CKD with overt proteinuria. Participants will be randomized into four groups (1:1:1:1): fimasartan standard SBP control (SBP < 140 mmHg); fimasartan strict SBP control (SBP < 130 mmHg); losartan standard SBP control; and losartan strict SBP control. After 24 weeks, all individuals are treated with fimasartan for an additional 120 weeks in an open-label design, maintaining their assigned SBP control groups as randomized. The primary endpoint is the rate of change in proteinuria, which is assessed using the spot urine albumin–creatinine ratio at 24 weeks. The secondary endpoints are the cardiovascular and renal outcomes at 144 weeks compared between the strict SBP and standard SBP control groups.

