**Discussion:**

The FANTASTIC is a clinical study to provide: (1) the reno-protective effect of fimasartan; and (2) the target BP to reduce adverse outcomes in hypertensive diabetic CKD with overt proteinuria.

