## Background

Hypertension affects approximately 40% of adults worldwide [1] and about two-thirds of patients with diabetes have concomitant hypertension [2]. Both hypertension and diabetes have a variety of vascular complications, including macrovascular and microvascular effects. The macrovascular complications of hypertension and diabetes include coronary artery disease, stroke, and peripheral vascular disease. The microvascular complications include retinopathy, nephropathy, and neuropathy. Hypertension and diabetes also increase the risk of developing new-onset chronic kidney disease (CKD) [3]. The progression of CKD is accompanied by microvascular complications. CKD increases a patient’s risk of stroke, coronary artery disease, and all-cause mortality. The annual mortality rate of those patients who progress to require dialysis is about 10–20% [4, 5].

Given the association between CKD and cardiovascular disease, it is important to suppress CKD progression in patients with both hypertension and diabetes. The degree of baseline proteinuria is correlated to the future progression of CKD [6–8]. High albuminuria was shown to be associated with increased risk of myocardial infarction, stroke, first hospitalization for heart failure, unstable angina, coronary or peripheral revascularization, and cardiovascular death [9]. Recent evidence has shown that reducing proteinuria can prevent the progression of CKD. Angiotensin II receptor blockers (ARB) have also been shown to reduce CKD progression of CKD [10–14]. Most hypertension guidelines recommend that angiotensin converting enzyme inhibitors (ACEI) or ARBs be used in patients with hypertensive diabetes [15–17]. There are few studies that directly compare the renal efficacy of two ARBs in hypertensive diabetes. In one comparison study of hypertensive type 2 diabetic patients with overt nephropathy, telmisartan were found to have similar renal efficacy to valsartan [18]. In another comparison study, telmisartan was found to be superior to losartan at reducing the geometric mean urinary protein–creatinine ratio without a change in blood pressure (BP), dietary sodium, or estimated glomerular filtration rate (eGFR) [19]. Therefore, although ARBs have a reno-protective class effect, there are relative differences in each drug’s efficacy.

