#### Randomization

The individuals are finally selected at baseline (Visit 3). An independent group not involved with study implementation creates a randomization schedule for study drug labelling and randomization is stratified by study site. Eligible participants are randomized into one of the following four groups in a 1:1:1:1 ratio using the interactive web-based randomization system, Fimasartan group A, Fimasartan group B, Losartan group A, and Losartan group B. Group A is a standard BP control group (SBP < 140 mmHg), while Group B is a strict BP control group (SBP < 130 mmHg). The randomized participants are treated with the investigational product (fimasartan or losartan) corresponding to each treatment group for 24 weeks on double-blind (physician and patient). After that, all individuals take fimasartan for an additional 120 weeks in an open-label study conducted with two groups (in accordance with BP control). The eligible participants provide written consent for participation in the open-label study and clinical study (Fig. 1).

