### Primary and secondary endpoints

The primary endpoint is the rate of change in proteinuria in the fimasartan group and the losartan group from baseline to 24 weeks.

The major secondary endpoints are cardiovascular composite endpoints and renal composite endpoints. The cardiovascular composite endpoints are defined as the time to the first occurrence of any of the following (in accordance with the BP control criteria): myocardial infarction; stroke; hospitalization due to heart failure; unstable angina; coronary revascularization; peripheral revascularization; or all-cause mortality. The renal composite endpoints include any of the following (in accordance with the BP control criteria): the time to serum creatinine concentration doubling from baseline; the time to progression to end stage renal disease (ESRD) (as confirmed by the initiation of long-term dialysis or renal transplantation); and all-cause mortality.

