### Statistics

In order to achieve a statistical power of 80%, the sample size assumed a non-inferiority margin of 18% (based on two-sided t test and a significance level of 0.025). This is based on the rate of change in proteinuria from baseline (Week 0) to week 24 of both losartan and fimasartan groups with a standard deviation of 62% [10, 12–14, 23]. Based on the assumption of a drop-out rate of 20%, a total of 468 patients are needed for randomization (with 234 patients per treatment arm).

The primary efficacy assessment finds that the fimasartan group is not inferior to the losartan group if the lower limit of a 95% two-sided confidence interval for the difference in the rate of change in proteinuria at week 24 between the fimasartan and losartan groups (control group - study group) is > − 18%. This is defined as the non-inferiority margin.

The major secondary efficacy assessment is determined by the incidence of combined cardiovascular and renal composite endpoints and is assessed using Kaplan–Meier curves, according with target BP at 144 weeks. The median survival time and confidence interval for the median survival time are presented. The log-rank test is used to compare the groups. Other secondary efficacy assessments are determined using the following methods. For continuous variables, descriptive statistics (number of individuals, mean, standard deviation, median, minimum, and maximum) for each time point are provided according to treatment group or the BP control criteria. The t-test is used to compare the inter-group difference in the rate of change. The inter-group difference in the amount of change is tested using the analysis of covariance, with the baseline values as covariates and the treatment groups as factors. The least squared mean and standard error are provided for each group. Frequencies and ratios are provided for categorical variables such as the proportion of individuals. For categorical variables, the Chi-square test, Fisher’s exact test, or Cochran–Mantel–Haenszel test is performed.

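### Major secondary composites: the named time-to-event summary is a median that will probably not be reached by week 144, and no between-group estimate with a confidence interval is named

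*Protocol article*

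**What the plan says.** The abstract's Methods paragraph sets the comparison: "The secondary endpoints are the cardiovascular and renal outcomes at 144 weeks compared between the strict SBP and standard SBP control groups". Under Primary and secondary endpoints, the cardiovascular composite is a time-to-first-event outcome that includes all-cause mortality and several non-fatal events. The renal composite covers creatinine doubling, end-stage renal disease and all-cause mortality.

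For these major secondary endpoints, the Statistics section says that the incidence "is assessed using Kaplan–Meier curves, according with target BP at 144 weeks". It continues: "The median survival time and confidence interval for the median survival time are presented". The test follows: "The log-rank test is used to compare the groups".

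The median is thus the only numerical time-to-event summary for which an interval is named. No hazard ratio, difference in risk or other contrast between target groups appears. The same section does name estimates elsewhere: a 95% CI for the group difference on the primary endpoint, and least-squares means with standard errors for amount of change.

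The abstract's Discussion paragraph lists, as one of two things the study is to provide, "the target BP to reduce adverse outcomes in hypertensive diabetic CKD with overt proteinuria".

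**The concern.** A Kaplan–Meier median can be read off only when the curve falls to 50%. In patients followed for under three years, with an eGFR of at least 30 and dialysis excluded, half of a group would need an event. If that does not happen, the one summary given an interval is blank in both groups. The reader then has curves, incidence and a log-rank p-value, but no size of the strict-versus-standard difference and no measure of its precision.

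That matters most if the log-rank test is not significant. Without an interval, a result compatible with a worthwhile benefit cannot be told apart from one that rules it out, and the blood-pressure target is one of the trial's two stated questions.

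**Working it through.** **Inputs from the article.** Follow-up is 144 weeks. The total is 468 patients with 20% drop-out (Statistics). Allocation is 1:1:1:1 (Randomization), so 468/2 = 234 per blood-pressure target when pooled over drug. The only rate given is in the Background: "The annual mortality rate of those patients who progress to require dialysis is about 10–20" per cent.

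**Assumption.** No composite event rate is given, so a constant annual risk r from 2% to 20% is used.

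**The plan's own figure.** With margin 18, SD 62, one-sided alpha 0.025 and 80% power:

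n = 2 × (1.96 + 0.842)² × 62² / 18² = 186.2, rounded up to 187 per drug arm

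187 / 0.8 = 233.75, so 234 per arm and 468 in total. This matches the article. It rests on proteinuria alone and says nothing about events.

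**Rate needed for a median.**

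T = 144 × 7 / 365.25 = 2.76 years

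1 − (1 − r)^T = 0.5 gives r = 1 − 0.5^(1/2.76) = 22.2% a year

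**Benchmark.** At the top of the dialysis mortality range, 1 − 0.80^2.76 = 46.0% by week 144. At the bottom, 1 − 0.90^2.76 = 25.2%.

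**Over the assumed range** (all 468 followed to week 144). Median = ln 2 / −ln(1 − r). Events d = 468 × risk. The hazard-ratio CI factor is exp(1.96 × 2/√d). The risk-difference half-width is 1.96 × √(2F(1 − F)/234), where F is the 144-week risk, taken as equal in both groups.

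| Annual risk | Risk by week 144 | Median (weeks) | Events | 95% CI for HR, ×/÷ | 95% CI for risk difference, ± points |
|---|---|---|---|---|---|
| 2% | 5.4% | 1790 | 25 | 2.18 | 4.1 |
| 5% | 13.2% | 705 | 62 | 1.65 | 6.1 |
| 10% | 25.2% | 343 | 118 | 1.43 | 7.9 |
| 15% | 36.1% | 223 | 169 | 1.35 | 8.7 |
| 20% | 46.0% | 162 | 215 | 1.31 | 9.0 |

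The expected median lies beyond week 144 in every row. The hazard ratio and risk difference can be estimated in every row. With 20% fewer patients (374), the hazard-ratio factor at 10% a year widens from 1.43 to 1.50.

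**Chance variation.** The binomial probability that at least half of a group has an event is 12% (234 patients) to 14% (187 patients) at 20% a year. It is below 0.01% at 15% and effectively nil at 10% or less.

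**Interval for the median.** A lower limit exists by week 144 if the lower 95% band of survival falls below 0.50.
- At 20% a year: 0.540 − 1.96 × √(0.46 × 0.54/234) = 0.476, so a lower limit would be expected.
- At 15% a year: 0.639 − 1.96 × √(0.361 × 0.639/234) = 0.577, so it would not.

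**The case against.** The strongest reply is that this is a condensed article. A hazard ratio and model details may well be in the full protocol or the SAP, neither of which is shown, and reporting a median as not reached does no harm. The first part stands: the missing hazard ratio alone would be no finding. But the article does not stay silent here. It chooses a summary measure and an interval, and the choice fits the design poorly.

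Several stronger readings are tempting and are not supported:

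- **That the median cannot be reached.** No composite rate is given. Dialysis mortality is not an upper bound on composites that also count non-fatal events. At 20% a year there is some chance of reaching 50%, and the lower confidence limit would usually exist.
- **That only a p-value would remain.** Incidence and Kaplan–Meier curves by target are planned. Albuminuria and eGFR endpoints by target, to week 144, are listed under Other secondary endpoints.
- **That the median is the plan's effect estimate.** A median per group is descriptive. What is not named is a contrast between groups.
- **That the log-rank test is wrong because it does not account for drug.** The article does not say whether the test is stratified. Drug is balanced over the targets by the 1:1:1:1 allocation, and "After that, all individuals take fimasartan for an additional 120 weeks".
- **That the trial fails on power for these endpoints.** The article claims no power for them.

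**Conclusion.** The concern holds in a limited form: the Statistics section fixes a poorly suited summary for the major secondary composites and names no strict-versus-standard estimate with a confidence interval. The median needs about 22% annual risk to appear by week 144. The article's only benchmark reaches 46% at most, and it comes from a sicker group than those enrolled. Not reached is therefore the probable result, but not a certain one.

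This rests on an assumed constant hazard and an assumed range of 2–20% a year. Composite rates of about 22% or more would change it, and the article neither gives nor excludes them. The interval widths in the table show what a better measure would deliver and are no criticism of the sample size. The point merits a change to the plan; it does not threaten the primary analysis or the validity of the log-rank test.

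**What to change.** In the Statistics section, for each composite by blood-pressure target:

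1. Make the main summary the hazard ratio, strict versus standard, with 95% CI from a Cox model. Adjusting or stratifying for randomised drug is optional.
2. Report the Kaplan–Meier event risk at 144 weeks in each target group, and the risk difference with 95% CI.
3. Keep the curves and the log-rank test. Report the median only if it is reached.
4. State that a non-significant log-rank test is interpreted from the confidence interval and is not evidence of equal outcomes.

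If the full protocol or SAP already specifies items 1 and 2, it is enough to align the article's description with it. The cost is slightly more analysis work, with no new data and no extra patients. The change should be fixed before outcomes by target group are examined.

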### Study eligibility

#### Inclusion and exclusion criteria

Patients are screened for the following four required conditions: high BP; CKD; overt proteinuria (or macroalbuminuria); and type 2 diabetes mellitus. The detailed inclusion criteria are described in Table 1. The exclusion criteria are described in Table 2. Finally, after learning about the study, patients voluntarily provided written consent to participate.

**Table 1 Tab1:** Inclusion criteria

Age: 19–70 years
Screening visit (Visit 1)
Hypertension in treatment-naïve patients
140 mmHg ≤ SBP < 180 mmHg and DBP < 110 mmHg
Hypertension with treatment, including ACEI/ARB
130 mmHg ≤ SBP < 180 mmHg and DBP < 110 mmHg
eGFR ≥ 30 mL/min/1.73 m^2^ (by MDRD) within the past six months
Urine protein (within the past six months)
ACR ≥ 300 mg/g (or mg/day)
or protein–creatinine ratio ≥ 500 mg/g (or mg/day)
Type 2 diabetes mellitus (diagnosed > 3 months prior) on medications with
no changes in medication regimen/dose within the last three months
Baseline visit (Visit 3)
Hypertension
140 mmHg ≤ SBP < 180 mmHg and DBP < 110 mmHg
eGFR ≥ 30 mL/min/1.73 m^2^ (by MDRD)
Urine protein: ACR ≥ 300 mg/g in spot urine
Type 2 diabetes without regimen change during placebo run-in period

*SBP* systolic blood pressure, *DBP* diastolic blood pressure, *ACEI* angiotensin converting enzyme inhibitor, *ARB* angiotensin receptor blocker, *ACR* albumin–creatinine ratio, *eGFR* estimated glomerular filtration rate, *MDRD* Modification of Diet in Renal Disease

**Table 2 Tab2:** Exclusion criteria

Secondary or malignant hypertension
Inter-arm BP difference: SBP > 20 mmHg or DBP > 10 mmHg
Symptomatic orthostatic hypotension
Cardiovascular history
MI, congestive heart failure (NYHA class III or IV), CABG, PTCA, or angina < 3 months before enrollment
Severe cerebrovascular disease (stroke, cerebral infarction, or cerebral hemorrhage)
Arrhythmia (significant ventricular tachycardia, atrial fibrillation, or atrial flutter)
Significant valvular disease: aortic stenosis or mitral stenosis
Hypertrophic cardiomyopathy
Type 1 DM or HbA1c > 9% at screening
Significant renal or hepatic disease
Dialysis, cirrhosis, biliary tract obstruction, cholestasis, or liver failure
eGFR (MDRD) < 30 mL/min/1.73 m2, hyperkalemia (>5.5 mmol/L) or hypokalemia (<3.5 mmol/L)
AST or ALT > 3 times the upper limit of normal

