### Blood pressure and biochemical measurements

The reported BP is the mean BP from three measurements on the selected arm. Proteinuria is measured from the spot urine albumin–creatinine ratio (ACR) based on the first urine in the morning. The eGFR is calculated using the modified Modification of Diet in Renal Disease (MDRD) equation [22].

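### The log-rank test named for the two 144-week composites uses no baseline covariates; it is valid, but adjusting for baseline ACR and eGFR could recover power at almost no cost

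*Protocol article*

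**What the plan says.** Under Primary and secondary endpoints: "The major secondary endpoints are cardiovascular composite endpoints and renal composite endpoints". Both are read by SBP target. The Statistics section says that their incidence "is assessed using Kaplan–Meier curves, according with target BP at 144 weeks", adds median survival times with confidence intervals, and then states: "The log-rank test is used to compare the groups". It names no covariates, strata or regression model for these endpoints.

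The Background describes what drives the risk of such events: "The degree of baseline proteinuria is correlated to the future progression of CKD", and "High albuminuria was shown to be associated with increased risk of myocardial infarction, stroke, first hospitalization for heart failure" (the sentence goes on to further cardiovascular events).

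Both candidate covariates are in hand. The baseline-visit criteria in Table 1 require "Urine protein: ACR ≥ 300 mg/g in spot urine" and an eGFR of at least 30 mL/min/1.73 m². The measurement section says: "The eGFR is calculated using the modified Modification of Diet in Renal Disease (MDRD) equation". Neither criterion has an upper limit. The Randomization section gives one balancing factor only: "randomization is stratified by study site".

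**The concern.** In a time-to-event comparison, leaving out a strong prognostic factor pulls the estimated hazard ratio towards 1 and lowers the power of the test, even when randomisation is perfect. Here the article itself points to such a factor. The entry criteria put a floor but no ceiling on ACR and eGFR, so baseline risk may vary widely.

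The SBP-target question is one of the trial's two stated aims, yet the sample size was set for the 24-week proteinuria comparison. Power for the composites is whatever that number happens to give, so efficiency matters more here than for the primary endpoint.

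**Working it through.** **1. The plan's own figure.** Inputs from Statistics: margin 18%, SD 62%, power 80%, alpha 0.025 (taken as one-sided), drop-out 20%; true difference taken as 0.

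n per arm = 2 × (1.96 + 0.84)² × 62² / 18² ≈ 187; 187 / 0.80 ≈ 234; total 468. This reproduces the stated 468 exactly, and it concerns the primary endpoint only. No event count or power is stated for the composites. The 1:1:1:1 allocation gives 234 per SBP target.

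**2. Rough power for the composites.** Schoenfeld: power = Φ(½√D × |ln HR| − 1.96). With 468 × 0.80 ≈ 374 patients' worth of follow-up and an assumed hazard ratio of 0.70:

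- 20% overall risk: D ≈ 75, power 34%.
- 30% overall risk: D ≈ 112, power 47%.
- Events for 80% power: 4 × (1.96 + 0.84)² / (ln 0.70)² ≈ 247.

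**3. What adjustment could add.** None of the next inputs is in the documents; all are assumptions. Trials were simulated with 468 patients, 144 weeks of follow-up, 20% exponential drop-out and two-sided alpha of 0.05. The unadjusted log-rank test was compared with the Wald test for SBP target in a Cox model that also held two baseline covariates (and, in the grid below, randomised drug). Covariate strength is the SD of their joint contribution to the log-hazard.

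*Moderate strength.* SD 0.7, conditional hazard ratio 0.60, 2,500 runs per cell:

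| Standard-group 144-week risk | Log-rank | Adjusted Cox | Gain (points) |
|---|---|---|---|
| 15% | 42% | up to 44% | about 2 |
| 25% | 61% | 65–67% | 4–6 |
| 35% | 75% | 79–82% | 4–7 |

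SD 0.7 corresponds to a hazard ratio of about 1.5 per doubling of ACR and 1.3 per 10 mL/min lower eGFR. With the covariate weights used (0.76 and 0.65), this implies a between-patient SD of 0.76 × 0.7 / (ln 1.5 / ln 2) ≈ 0.91 for log ACR and 10 × 0.65 × 0.7 / ln 1.3 ≈ 17 mL/min for eGFR.

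*Wider grid.* Standard-group risk 10, 20, 30 and 40%; hazard ratio 0.6, 0.7 and 0.8; 1,000 runs per cell:

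| Log-hazard SD | Gain over log-rank, lowest to highest cell (points) |
|---|---|
| 0 | −1.2 to +0.3 |
| 0.5 | −1.1 to +3.3 |
| 1.0 | −0.3 to +16.1 |
| 1.5 | +0.8 to +30.1 |

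The small negative values lie within simulation noise: the standard error of one power estimate is at most √(0.25/1000) ≈ 1.6 points. At 10% risk (34 to 39 events) no cell gained more than 4.6 points. The top value is hazard ratio 0.6, risk 40%, SD 1.5: 58.4% against 88.5%.

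The large gains need strong covariates. Scaling the SD 0.7 translation to SD 1.3 gives 1.5^(1.3/0.7) ≈ 2.1 per doubling of ACR and 1.3^(1.3/0.7) ≈ 1.6 per 10 mL/min.

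**4. Validity.** At hazard ratio 1.0 (1,500 runs per cell) both tests rejected in 4.3 to 6.1% of trials, in line with the nominal 5%.

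**5. Randomised drug as the only prognostic factor.** With a drug hazard ratio of 0.8 applied throughout follow-up, an SBP-target hazard ratio of 0.7, 30% risk and 2,000 runs: log-rank 43.5%, adjusted 43.3%. No gain.

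**The case against.** The strongest reply is that nothing here is wrong. The log-rank test is standard, controls type I error, needs no covariate functional form and answers a marginal question. Chance imbalance in ACR or eGFR is already covered by its error rate. Part of the apparent shrinkage of the unadjusted hazard ratio is non-collapsibility, a difference in what is estimated rather than bias. An analysis plan that is not shown may add a stratified test or a Cox model. All of this stands. It makes the point one of efficiency, not validity, and rules out saying that the authors decided against adjustment. It does not remove the point, because the article does name a test, and a better one can be built from data already collected.

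Some stronger readings are tempting but unsupported:

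- **A definite power loss.** The Background gives associations in words only. Any single figure or narrow range is an assumption, and the same covariate strength need not hold for both composites.
- **Leaving out randomised drug costs power.** Drug is balanced 1:1 within each SBP target and differs for only 24 of 144 weeks. The simulation showed no gain.
- **Site specialty should enter the model.** The article counts nephrology, cardiology and endocrinology centres but says nothing about differing event rates.
- **Inconsistency with the ANCOVA for amount of change.** That model adjusts an outcome for its own baseline value. A time-to-first-event composite has none. The same section also uses an unadjusted t-test for rate of change, so there is no general rule to breach.

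**Conclusion.** The point holds as an efficiency improvement on the major secondary endpoints. The only named test leaves out baseline measures of which one, albuminuria, the article itself calls prognostic. The possible loss runs from nothing to about 30 points, with about 2 to 7 at the moderate strength above; which applies depends on event risk, true effect and covariate strength, none of which the documents give. In the simulations adjustment cost at most about a point, within noise, so the balance favours it.

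A reader might infer that adjustment would make the SBP-target comparison adequately powered. It would not for modest effects: at hazard ratio 0.7 and 30% standard-group risk, adjusted power stayed at about 45 to 49% whatever the covariate strength.

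**What to change.** In Statistics, or in the analysis plan, pre-specify for each composite a Cox model containing randomised SBP target, log baseline ACR and baseline eGFR, both from the baseline visit. Make the SBP-target term the main test, and report its hazard ratio with a 95% confidence interval. Keep the Kaplan–Meier curves and the unadjusted log-rank test as supportive. This also supplies an effect estimate, which the log-rank test does not.

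The cost is wording only: no extra patients, visits or measurements. There are two small downsides. The hazard ratio is conditional on the covariates, so reports must say so. The functional form (log ACR, linear eGFR) must be fixed before outcome data by SBP group are examined. If an existing analysis plan already specifies an adjusted model, the two texts need only be aligned on which analysis is the main one.

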### Screening

Included individuals go through a single-blind placebo run-in period for at least four weeks. During this period, any treatment with ACEI/ARBs for hypertension will be discontinued. However, other antihypertensive drugs are administered without changing the regimens or doses. During the placebo run-in period, the participant is instructed to measure his/her own BP with a provided oscillometric automatic device more than once a day. Individuals are instructed to visit the study site in the event of SBP ≥ 180 mmHg or onset of any symptoms of suspected hypertension (e.g. headache, dyspnea, chest discomfort, vomiting, and neurologic symptoms). In this situation, additional antihypertensive drugs (other than ACEIs/ARBs) are introduced or adjustments were made to the doses of the patient’s other medications as appropriate. After the placebo run-in period is completed for at least four weeks, tests for eligibility assessment are performed at the visit before baseline (Visit 2).

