### Other secondary endpoints

The other secondary endpoints are summarized as follows: (1) the rate of change in proteinuria in the fimasartan and losartan groups from baseline to weeks 4, 8, and 12; (2) the change in proteinuria in the fimasartan and losartan groups from baseline to weeks 4, 8, and 12; (3) the rate and amount of change in eGFR in the fimasartan and losartan groups from baseline to weeks 4, 8, 12, and 24; (4) the proportion of individuals who developed microalbuminuria (urine ACR < 300 mg/g) in the fimasartan and losartan groups at weeks 4, 8, 12, and 24; (5) the proportion of individuals with ≥ 30% decrease in albuminuria in the fimasartan and losartan groups from baseline to weeks 4, 8, 12, and 24; (6) the proportion of participants with ≥ 50% decrease in eGFR in the fimasartan and losartan groups from baseline to weeks 4, 8, 12, and 24: (7) the rate and amount of change in albuminuria from baseline to weeks 4, 8, 12, 24, 36, 48, 72, 96, 120, and 144 in accordance with the BP control criteria; (8) the rate and amount of change in eGFR from baseline to weeks 4, 8, 12, 24, 36, 48, 72, 96, 120, and 144 in accordance with the BP control criteria; (9) the proportion of individuals with a change in microalbuminuria (urine ACR < 300 mg/g) at weeks 4, 8, 12, 24, 36, 48, 72, 96, 120, and 144 in accordance with the BP control criteria; (10) the proportion of participants with ≥ 30% decrease in albuminuria from baseline to weeks 4, 8, 12, 24, 36, 48, 72, 96, 120, and 144 in accordance with the BP control criteria; and (11) the proportion of individuals with ≥ 50% decrease in eGFR from baseline to weeks 4, 8, 12, 24, 36, 48, 72, 96, 120, and 144 in accordance with the BP control criteria.

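### Albuminuria and eGFR percent change is tested visit by visit with an unadjusted t-test; one baseline-adjusted repeated-measures model (log ACR for albuminuria) would be better (minor, other secondary endpoints)

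*Protocol article*

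**What the plan says.** The Other secondary endpoints section lists changes from baseline at separate visits. Items (1) to (3) compare the drugs up to week 12 for proteinuria and week 24 for eGFR. Items (7) and (8) compare the BP targets at ten visits: "the rate and amount of change in albuminuria from baseline to weeks 4, 8, 12, 24, 36, 48, 72, 96, 120, and 144" and "the rate and amount of change in eGFR from baseline to weeks 4, 8, 12, 24, 36, 48, 72, 96, 120, and 144".

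The Statistics section gives descriptive statistics "for each time point are provided according to treatment group or the BP control criteria". It then names two tests:

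- Rate of change: "The t-test is used to compare the inter-group difference in the rate of change", with no covariate.
- Amount of change: "The inter-group difference in the amount of change is tested using the analysis of covariance, with the baseline values as covariates", with least-squares means.

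It names no longitudinal model and no eGFR slope. The article does not define rate of change. I read it as percent change, because the margin (18%) and standard deviation (62%) for the primary endpoint are percentages. That the tests are done visit by visit follows from how the endpoints are defined; the t-test sentence does not say so itself.

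Two other statements bear on the BP-target comparison. In the run-in, "any treatment with ACEI/ARBs for hypertension will be discontinued", so baseline is measured off these drugs. Under Methods of dose administration, patients who cannot tolerate the BP control process leave the study.

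**The concern.** The same data on the same question get an adjusted test on one scale and an unadjusted test on the other, and the article gives no reason. Three things are at stake, in decreasing order of how firmly the text supports them.

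1. **Power for albuminuria.** Percent change in ACR is bounded below at -100% and has a long upper tail. A t-test on it, without baseline, wastes information.
2. **Early and late eGFR change.** All patients start an ARB after baseline and are titrated to different SBP targets, so early treatment intensity differs by BP target by design. Each eGFR endpoint is change from baseline and therefore contains any early difference, although the stated aim is the long-term effect of strict control.
3. **Drop-out.** Leaving the study can depend on the BP target. A visit-wise test on whoever has data does not use the earlier measurements of those who left.

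**Working it through.** **The plan's own figure.** Inputs from Statistics: margin 18, SD 62, power 80%, and a 95% two-sided interval (one-sided 0.025).

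n = 2 × (1.96 + 0.8416)² × 62² / 18² = 186.2, so 187 per arm. Then 187 / 0.8 = 233.75, so 234 per arm and 468 in all. This matches the plan. With 1:1:1:1 allocation, the BP-target comparison also has 234 against 234.

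**Albuminuria, plan's method.** The detectable difference at two-sided 0.05 and 80% power is 2.80 × 62 × √(2/n): 18.0 points with n = 187, 19.2 with 164 and 20.8 with 140.

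**Albuminuria, baseline adjustment of percent change.** Multiply by √(1 - r²), where r is the correlation of baseline with percent change (assumed). For r = 0.1, 0.3 and 0.5, 18.0 becomes 17.9, 17.1 and 15.6.

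**Albuminuria, log scale alone.** Assume the follow-up/baseline ratio is log-normal with the plan's SD of 0.62 and an average mean ratio μ, with arm means 0.18 apart (80% power for the t-test).

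- Log SD: s = √ln(1 + (0.62/μ)²). Log difference: d = ln[(μ + 0.09)/(μ - 0.09)]. Then z = d / (s√(2/187)).
- μ = 1.0: s = 0.570, d = 0.180, z = 3.06, power about 86%.
- μ = 0.8: s = 0.686, d = 0.226, z = 3.19, power about 89%.

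A simulation that also adjusts for baseline log ACR (187 per group; assumed ACR inputs giving a percent-change SD of about 51-59%) raised power from 80-88% to 92-95%.

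**eGFR, baseline adjustment of percent change.** With assumed baseline mean 55 and SD 15, residual SD 5, slope SD 3.5 per year and baseline at least 30, r is about 0.09. Then 1 - 0.09² = 0.992, a variance cut of about 1%.

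**eGFR, early difference.** Suppose the strict arm has an early drop larger by D mL/min/1.73 m² (assumed). It cancels an annual benefit of D / (weeks/52).

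| D | Week 48 | Week 144 |
|---|---|---|
| 1 | 1.1 per year | 0.4 per year |
| 2 | 2.2 per year | 0.7 per year |
| 3 | 3.3 per year | 1.1 per year |

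Simulation with the eGFR inputs above, 234 per BP arm, about 20% lost by week 144 and slopes of -4 against -3 per year:

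| Early effect in strict arm | Week-144 t-test power | Slope-model power |
|---|---|---|
| 0 | 56% | 67% |
| -1.5 | 17% | 69% |
| -3 | 5% | 68% |

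With no early effect, ANCOVA on the amount of change had 61%. With an early effect of -3 and equal slopes, the t-test rejected in 65% of runs and the slope model in 6%. The slope model here started at week 12.

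**Drop-out, no true effect, tests limited to patients with week-144 data.**

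- Strict arm loses more decliners (76% against 87% retained): bias of about +3 points. The t-test rejected in 25% of runs, ANCOVA in 23%, the slope model in 5.5%.
- Standard arm loses more decliners (about one third missing overall): bias of -2.6 points. The t-test rejected in 18%; a repeated-measures estimate was essentially unbiased.

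The sign reverses with the arm that loses decliners. In both set-ups drop-out depends on observed eGFR, which is the condition under which likelihood-based models are valid, so their good performance follows from the set-up.

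**The case against.** The strongest objection is that much of the case rests on things the article does not say.

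- **Missing data.** A reader might infer that each test uses only patients still present. The article names neither an analysis set nor a missing-data rule for these endpoints, and a condensed article may leave both to the full protocol or analysis plan. The objection stands: drop-out bias is a conditional risk. The drop-out allowance in the document is 20% ("Based on the assumption of a drop-out rate of 20%, a total of 468 patients are needed for randomization"), with no separate figure for week 144.
- **Adjustment.** A reader might infer that all these analyses are unadjusted. They are not: the amount of change has ANCOVA. The variance formula (1 + ρ)/2, which gives 10-25% for correlations of 0.8 to 0.5, concerns raw change scores and so does not describe the t-test on percent change.
- **Early drop.** A reader might infer that a repeated-measures model removes it. It does not, because each contrast is still change from baseline. Only the slope separates early from late, and a slope starting at week 24 sets aside part of the randomised effect. Total change from baseline is a legitimate target of estimation, and the listed visits show early and late change side by side.
- **Importance.** These are other secondary endpoints. The major BP-target comparisons use the time-to-event composites and the log-rank test.

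What survives is that the article itself names the t-test, so the weakness is in a stated method and not in an omitted detail.

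**Conclusion.** The point holds as a minor one. The plan fixes an unadjusted t-test on percent change, applied to endpoints defined visit by visit, where a baseline-adjusted repeated-measures model on data already collected would do better.

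- **Albuminuria:** the gain is material, illustratively from 80-88% to 92-95% power. It assumes roughly log-normal ACR.
- **eGFR:** baseline adjustment of percent change gains next to nothing. The reason to change is the use of all visits, plus a supportive view of the long-term slope.
- **Drop-out by BP target:** possible from the withdrawal rule, but its direction and size are unknown.
- **Early eGFR difference:** carried into every visit by construction. Its size is not in the document, so the figures shown give direction and range only.

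The documents do not support the stronger conclusion that the 144-week BP-target evidence as a whole is biased. The cardiovascular and renal composites do not depend on these tests.

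**What to change.** For items (1) to (3), (7) and (8), replace the visit-wise t-test and ANCOVA with one mixed model for repeated measures per outcome: log ACR for albuminuria, and eGFR or log eGFR. Include baseline by visit, drug, BP target, site, visit and group by visit. Report the contrast at each listed visit from that model, back-transformed to percent where a rate of change is wanted.

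Add the eGFR slope from week 24 to week 144 by BP target. Label it supportive, not a replacement for change from baseline.

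Cost: analysis wording and programming, with no new data. The model is slightly more complex and relies on a missing-at-random assumption. The albuminuria result becomes a geometric instead of an arithmetic mean percent change, and there is one extra supportive estimate to report.
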